### Randomization and blinding

Included patients participated in no more than two treatment cycles. Women meeting the inclusion criteria will be randomized according to an online central randomization database (www.medresman.org) in a 1:1 ratio on the day of stimulation. The online sequence is generated and input into the online central randomization system by the staff members who are not involved in enrolling subjects. It is not accessible to any investigators or study coordinators. If a subject fulfills the enrollment criteria, the authorized investigator will log in to the password-protected account to get the assignment. After randomization, patients will be blinded to group allocation and randomly assigned to one of two groups: the control group (traditional flexible GnRH antagonist protocol) or the experimental group (LH-based flexible GnRH antagonist protocol). The nature of the treatment interventions precludes blinding of treating physicians. However, this study will be blinded to embryologists, laboratory technicians, and nurses who conduct follow-ups until the completion of the statistical analysis of this study.

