### Sample size calculation

According to the literature and data from our center, the cumulative ongoing pregnancy rate per cycle in women with PCOS in the control arm was around 80%. Considering that a non-inferiority threshold should retain 80% of the clinical effect of a control treatment, a minimum clinical difference of 16% (two-sided: *α*, 2.5%; *β*, 20%) and a total of 196 patients were needed. Considering a possible withdrawal rate of 10%, the total number of patients required will be 216.

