#### Ovarian stimulation

The ovarian stimulation is initiated from days 2 to 3 of the menstrual cycle. Baseline pelvic ultrasound and serum E_2_, FSH, LH, progesterone (P), and beta-human chorionic gonadotropin (β-hCG) were measured. Recombinant FSH (rFSH; Gonal-f, Merck, Germany) at a dose of 150–300 IU/day is administered depending on patient age, body mass index (BMI), anti-Mullerian hormone (AMH), antral follicle count (AFC), and basal serum FSH concentration. Five days later, the doses are adjusted according to ultrasound examination, follicle development, and serum hormone levels.

For the traditional flexible GnRH antagonist protocol, GnRH antagonist (Cetrotide, 0.25 mg per day; Merck, Germany) is initiated and continued up until and including the day of trigger, once the E_2_ concentration is ≥ 300 pg/mL or the leading follicle reaches a size of 14 mm.

For the LH-based flexible GnRH antagonist protocol, the timing and dosage of antagonist administration are based on the serum LH levels from day 5 of ovarian stimulation. The blood test will be performed 3–4 times until trigger. No antagonist is administered if the LH level was ≤ 4 IU/L. 0.125 mg of cetrorelix acetate is administered daily if the LH concentration is > 4 IU/L and ≤ 6 IU/L, until the next blood test. 0.25 mg of cetrorelix acetate is administered daily if the LH concentration was > 6 IU/L and ≤ 10 IU/L, until the next blood test. If the LH concentration is > 10 IU/L and ≤ 15 IU/L, 0.375 mg of cetrorelix acetate is administered daily for 1 day. If the LH concentration is > 15 IU/L, 0.5 mg of cetrorelix acetate is administered for 1 day. The need for antagonist co-treatment is dependent on an LH concentration of > 4 IU/L until the day of trigger. After two or more follicles reach a diameter ≥ 18 mm, 0.2 mg triptorelin and 2000–3000 IU of hCG will be injected. Serum LH, E_2_, and P concentrations are measured.

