### Statistical analysis

Data analysis of this trial will follow the intention-to-treat principle, including a preliminary comparison of all randomized women in the two groups who did not drop out of the study. Differences between the groups will be compared between demographic variables and baseline information from before the start of the study. Continuous data with normal distribution will be estimated using a two-sample *t*-test, and the Mann-Whitney *U* test will be used for non-normally distributed data. Categorical data will be represented as frequency and percentage, and the differences in these variables will be assessed by the chi-square test or Fisher’s exact test. We will also compute the unadjusted risk ratio (RR) and its 95% confidence interval (CI). This test for non-inferiority will only be performed for the primary outcome; all other secondary outcomes will be tests of superiority. The primary outcome—cumulative ongoing pregnancy rate per cycle in women with PCOS in the control arm—was 80% in our center. Considering that a non-inferiority threshold should retain 80% of the clinical effect of a control treatment, the minimum clinical difference should be 16%. Noninferiority is declared if the upper limit of the two-sided 95% CI for the cumulative ongoing pregnancy rate in the study group does not exceed a relative margin of 16%, equivalent to a two-sided test with an *α* value of 2.5%. A two-sided *α* value of 0.05 is used for superiority testing.

In case of missing values of baseline characteristics, we will analyze them by excluding the missing values, then assign the missing values multiple times, and conduct subsequent analyses to estimate the robustness of the results. For follow-up loss and protocol violation, we will attempt sensitivity analysis to explore the influence of these factors on the trial results.

The flow chart of this study is given in Fig. 1. A schedule of enrollment, interventions, and assessment is provided in the Standard Protocol Items: Recommendations for Interventional Trials (SPIRIT) figure (Fig. 2), and the SPIRIT reporting guidelines are used as shown in Additional file 1 [14].

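### The only between-arm comparison the article names for the primary outcome is unadjusted, so a modest, low-cost gain in precision from known baseline values goes unused

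*Protocol article*

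**What the plan says.** **Analysis.** The Statistical analysis section of the protocol article assigns categorical outcomes to a chi-square or Fisher's exact test and then states: "We will also compute the unadjusted risk ratio (RR) and its 95% confidence interval (CI". It names no adjusted comparison. It also plans to compare baseline variables between the groups. Missing baseline values are to be excluded first and then multiply imputed to gauge robustness.

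**Allocation.** Under Randomization and blinding: "Women meeting the inclusion criteria will be randomized according to an online central randomization database (www.medresman.org) in a 1:1 ratio". No stratification factor or minimisation is named.

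**What is known before treatment.** Under Ovarian stimulation, the starting FSH dose is chosen "depending on patient age, body mass index (BMI), anti-Mullerian hormone (AMH), antral follicle count (AFC), and basal serum FSH concentration". Under Eligibility criteria, women aged 20 to 38 entering a first or a second cycle may join, so age and cycle number are also known at entry.

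**Design figures.** The Sample size calculation section says "the cumulative ongoing pregnancy rate per cycle in women with PCOS in the control arm was around 80" per cent, and continues with "a minimum clinical difference of 16% (two-sided: *α*, 2.5%; *β*, 20%) and a total of 196 patients were needed".

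**The concern.** In a two-arm trial with a binary outcome, baseline values that predict the outcome can be used to narrow the confidence interval without more patients. Here that interval decides non-inferiority, and the design has 80% power with almost nothing in reserve. The values are already part of clinical work-up, and simple 1:1 allocation does not balance them by design.

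The choice is explicit, since the article uses the word unadjusted. It also sits oddly with the imputation step. Imputing a baseline value leaves the outcome counts by arm as they were, so it cannot change an unadjusted risk ratio. It can affect the treatment comparison only through a model that uses baseline values, and no such model is named. Naming one in advance would give the imputation a purpose and leave no doubt about which covariates were chosen and when.

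**Working it through.** **Inputs.** Event rate 80% (Sample size calculation), taken as the same in both arms. Margin 16%, taken here as absolute points. Power 80%. Evaluable total 196, that is 98 per arm. One-sided 2.5%, the level implied by the two-sided 95% CI in the Statistical analysis section.

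**Step 1: reproduce the plan's figure without covariates.**

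n per arm = [0.8 × 0.2 + 0.8 × 0.2] × (1.960 + 0.842)² / 0.16² = 0.32 × 7.849 / 0.0256 = 98.1, so the total is 196.2. The stated 196 is reproduced. The planned size therefore belongs to an unadjusted analysis and reaches 80% power with one.

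**Step 2: effect of adjustment.** Let R² be the share of outcome variance explained by the baseline covariates. The variance of the risk difference is then multiplied by (1 − R²), as an approximation:

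- SE = √[0.32 × (1 − R²) / 98]
- Power = Φ(0.16 / SE − 1.96)
- CI half-width = 1.96 × SE
- Total for 80% power = 196.2 × (1 − R²)

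Unadjusted: SE = √(0.32 / 98) = 0.0571, and Φ(2.80 − 1.96) = Φ(0.84) = 80.0%. The article gives no R², so the rows below with R² above 0 are assumptions.

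| R² (assumed) | Power at 98 per arm | 95% CI half-width (points) | Total for 80% power |
|---|---|---|---|
| 0 | 80.0% | 11.2 | 196 |
| 0.02 | 80.7% | 11.1 | 192 |
| 0.05 | 81.9% | 10.9 | 186 |
| 0.10 | 83.9% | 10.6 | 177 |
| 0.15 | 85.9% | 10.3 | 167 |

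**Step 3: what these R² values require.** A simulation with a normally distributed baseline score in a logistic model, at an 80% event rate, gives R² of about 0.02 for an AUC of about 0.60, 0.04 for 0.64, 0.08 for 0.69 and 0.13 for 0.75. The upper end of the table therefore needs a rather good predictor.

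**Step 4: chance imbalance.** The part of the unadjusted estimate's random error that comes from imbalance in these covariates has SD 5.71 × √R² points: 0.8, 1.3 and 1.8 points at R² of 0.02, 0.05 and 0.10. Multiplied by 1.96, these are shifts of about 1.6, 2.5 and 3.5 points, exceeded in 1 trial in 20. The unadjusted CI already allows for this error; adjustment reduces it.

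**Step 5: dependence on the margin's scale.** The Statistical analysis section declares non-inferiority if the limit "does not exceed a relative margin of 16" per cent. If that is read as 16% of 80%, or 12.8 points, unadjusted power at 196 is Φ(0.128 / 0.0571 − 1.96) = 61%. R² of 0.02 to 0.15 raises it only to 62% to 68%.

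**The case against.** The strongest reply is that nothing here is wrong. An unadjusted comparison is valid under 1:1 randomisation, agrees with the sample-size calculation and ignores no stated design factor. An adjusted analysis may also sit in a statistical analysis plan that is not shown, and naming an unadjusted risk ratio does not rule one out. All of this stands, and it is why the point is a missed gain and not a defect.

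It also stands that the size of the gain is unknown. A reader might infer that the recorded values are strong predictors, because clinicians use them to choose the FSH dose. The documents do not support this: no association between any baseline value and cumulative ongoing pregnancy is given, and restricting entry to PCOS, ages 20 to 38 and first or second cycles may weaken prediction. Nor is baseline LH among the listed dose factors, though it is measured.

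A reader might further infer that adjustment would remove chance imbalance, or that comparing baseline variables shows an intention to adjust after seeing differences. Adjustment only reduces the part due to measured covariates, and the article announces no imbalance-driven adjustment.

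Finally, the Trial status section reports more than 180 women enrolled, and treating physicians are not blinded. A late change to the primary analysis needs care. That limits when and by whom the model may be chosen, but does not argue against fixing one before outcomes are examined.

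**Conclusion.** The point holds as an efficiency recommendation. The only primary comparison that the article names is unadjusted, no stratification is described, and several baseline values that may be prognostic are known before treatment. Prespecified adjustment would add about 1 to 4 power points for assumed R² of 0.02 to 0.10, and about 6 points at 0.15. The CI half-width would shrink by about 0.1 to 0.6 points over the first range and by about 0.9 points at 0.15.

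These figures rest on 80% in both arms, 98 evaluable women per arm, a 16-point absolute margin and the (1 − R²) approximation. They do not show that the planned analysis is invalid or that the trial misses its stated power without adjustment. Adjustment would also not make up for the loss of power if the margin proves to be relative.

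**What to change.** Before outcomes are examined, and with the choice made by people who have not seen them by arm, prespecify the following:

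- **Primary estimate:** a marginal (standardised) risk difference from a logistic model with arm, age, BMI, AMH or AFC, and first versus second cycle, averaged over the women in the primary analysis set. An adjusted odds ratio would not fit the margin.
- **Interval:** a robust or bootstrap two-sided 95% CI.
- **Missing baseline values:** the multiple imputation already planned.
- **Supportive analysis:** the unadjusted estimate.
- **Decision:** compare the CI with the margin on one scale, after reconciling the 16% used as absolute in the Sample size calculation section with the 16% called relative in the Statistical analysis section. If the agreed scale is a ratio, the same two standardised risks give it.

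The cost is a little more analysis work and no new data. The covariate list must stay short: at an 80% success rate, 196 women give only about 196 × 0.2 = 39 non-events for a model with arm plus four covariates, so the CI's small-sample behaviour should be checked in advance.

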**Methods/design:**

In this randomized, single-center, non-inferiority trial, we aim to test the hypothesis that there is no significant difference in cumulative ongoing pregnancy rates between PCOS patients stimulated with LH-based flexible protocol versus traditional flexible GnRH antagonist protocol. The primary efficacy endpoint will be the cumulative ongoing pregnancy rate per cycle. The secondary outcomes will be clinical pregnancy rate, cancelation rate, serious OHSS rate, and cost-efficiency. The cumulative ongoing pregnancy rate per cycle in PCOS women was 80%. Considering that a non-inferiority threshold should retain 80% of the clinical effect of a control treatment, a minimal clinical difference of 16% (two-sided: *α*, 2.5%; *β*, 20%) and a total of 196 patients were needed. Anticipating a 10% dropout rate, the total number of patients required was 216.

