
## Methods/design

### Study design and recruitment

This is a single-blind, non-inferiority, randomized controlled trial. Patients participating in the trial are undergoing their 1st or 2nd in vitro fertilization (IVF)/intracytoplasmic sperm injection (ICSI) cycle in Beijing Chao-Yang Hospital, Capital Medical University. The research project was approved by the Ethics Committee of Beijing Chao-Yang Hospital and was conducted in accordance with Good Clinical Practices. The study was registered on ClinicalTrials.gov (No: ChiCTR1800018129). Potentially eligible women will be given information about the study at their first consultation. Screening for eligibility will be performed by an authorized investigator on day 2 of the menstrual cycle, after obtaining informed consent from all eligible participants. The study is currently recruiting patients and is expected to be completed by 31 December 2022.

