### Outcome measures

The primary outcome will be the cumulative ongoing pregnancy rate resulting from one ART aspiration cycle, including fresh and FET cycles. Ongoing pregnancy is defined by the presence of a gestational sac with a fetal heartbeat after 12 weeks of gestation. The cycle in which no oocytes are retrieved or no embryo is available for transfer will be considered as not getting pregnant. Secondary outcomes will be high-quality embryo rate, clinical pregnancy rate, severe OHSS rate, and cancelation rate. Moreover, differences in cost-effectiveness and adverse events will be evaluated. Typically, a high-quality embryo is defined as an embryo with 7–10 cells and ≤ 25% fragmentation developed from 2PN embryos on day 3 after oocyte aspiration. The clinical pregnancy rate is defined as the presence of a gestational sac at 6–7 weeks of gestation when visualized by transvaginal ultrasound. Moderate OHSS is diagnosed when ovarian enlargement of > 5 cm and < 12 cm is observed and when ultrasonographic ascites are present with or without nausea, vomiting, and/or diarrhea. Severe OHSS is diagnosed when ovarian enlargement of ≥ 12 cm is observed and when there is clinical evidence of ascites and/or hydrothorax or breathing difficulties with or without hemoconcentration, severe hypoproteinemia, abnormal liver function, coagulation abnormalities, or diminished renal function.

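### The non-inferiority rule tests the wrong confidence limit of the wrong quantity, so taken literally it can pass only a grossly inferior protocol

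*Protocol article*

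**What the plan says.** The protocol article describes the design plainly: "This is a single-blind, non-inferiority, randomized controlled trial". Under Outcome measures, "The primary outcome will be the cumulative ongoing pregnancy rate resulting from one ART aspiration cycle, including fresh and FET cycles", so a higher value is better.

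The Sample size calculation section puts the control rate at about 80%, asks that 80% of the control effect be retained, and arrives at "a minimum clinical difference of 16% (two-sided: *α*, 2.5%; *β*, 20%) and a total of 196 patients were needed". The Statistical analysis section repeats this derivation of the 16%.

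The Statistical analysis section then gives the decision rule: "Noninferiority is declared if the upper limit of the two-sided 95% CI for the cumulative ongoing pregnancy rate in the study group" must not exceed a margin of 16%, which the sentence calls relative. It equates this to a two-sided test at 2.5%. The sentence names no difference or ratio, no control arm and no direction of subtraction. A risk ratio with its 95% CI is mentioned in the same section but is not tied to the non-inferiority decision. No other section gives a decision rule.

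The abstract states the hypothesis differently: "we aim to test the hypothesis that there is no significant difference in cumulative ongoing pregnancy rates".

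**The concern.** For a favourable outcome, an inferior treatment shows itself in the lower limit of study minus control. Non-inferiority requires that limit to stay above minus the margin. The rule uses the upper limit, which is the wrong side for any study-minus-control or study/control contrast. It also attaches that limit to the rate in one arm, so no comparison is made.

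This sentence decides whether the trial succeeds. As worded, it does not control the chance of calling a worse protocol non-inferior, and it leaves the operative reading to be settled later. Treating physicians are not blinded, an interim analysis is planned, and more than 180 women had already been enrolled when the article was prepared.

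The abstract does not help, because failing to find a significant difference does not demonstrate non-inferiority.

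**Working it through.** **Inputs.** Control rate 80%, margin 16%, power 80% and total 196 (Sample size calculation); 1:1 allocation (Randomization and blinding), hence 98 per arm; two-sided 95% CI (Statistical analysis). The study-group rate used for planning is not stated. It is assumed to be 80%, which the 196 implies.

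**1. Reproduce the planned sample size.** For an absolute margin of 16 points and one-sided 2.5%:

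n per arm = 2 × 0.80 × 0.20 × (1.960 + 0.842)² / 0.16² = 98.1

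This gives 196 in total, and 196 × 1.1 = 216 (rounded). The planned size therefore comes from the standard rule: lower limit of study minus control above -16 points.

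**2. Operating characteristics of that standard rule, 98 per arm.**
- True rates 80% vs 80%: SE = √(2 × 0.16/98) = 0.0571, and Φ(0.16/0.0571 − 1.96) ≈ 0.80. Exact binomial enumeration gives 80.0%.
- True rates 64% vs 80%, at the margin: 2.5%.

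**3. The rule taken literally: upper 95% limit of the study-group rate at most 16%.** The Clopper-Pearson upper limit is 15.5% for 8/98 and 16.7% for 9/98. The rule is met only with 8 or fewer pregnancies in 98 (8.2%). With a Wilson interval the cut-off is the same, and the chance of passing is about 0 at true study rates from 50% to 90%, 34% at 10% and 94% at 5%.

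**4. Read as the upper limit of study minus control at most +16 points.** At 64% vs 80%:

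SE = √((0.64 × 0.36 + 0.80 × 0.20)/98) = 0.0631

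P(declare) = Φ((0.16 + 0.16)/0.0631 − 1.96) = 0.999

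**5. Side by side.** Control 80%, 98 per arm, exact binomial enumeration with Wald intervals for the difference and log-normal intervals for the risk ratio:

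| Rule | Study 90% | Study 80% | Study 64% | Study 60% |
|---|---|---|---|---|
| Lower limit, study − control, > −16 points (same as upper limit, control − study, < 16) | 99.9% | 80.0% | 2.5% | 0.5% |
| Upper limit, study − control, ≤ +16 points | 23.1% | 80.0% | 99.9% | 99.98% |
| Upper limit, risk ratio study/control, ≤ 1.16 | 9.0% | 55.9% | 98.8% | 99.7% |

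Under the second and third rules the chance of success rises as the study protocol gets worse.

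**6. A worked result.** Suppose 58/98 (59.2%) in the study group and 78/98 (79.6%) in control. The difference is −20.4 points, 95% CI −33.0 to −7.8. The upper limit lies below +16, so the second rule declares non-inferiority although the interval shows significant inferiority. The standard rule fails it, because −33.0 is below −16.

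**The case against.** The strongest reply is that the intended rule can be recovered. The 16% is derived in the preceding sentence as a loss from the control rate, so a comparison with control is implied. The upper limit of control minus study below 16 points is mathematically the correct rule. The stated 196 reproduces from it and not from the alternatives tried: two-sided 2.5% gives 238, one-sided 5% gives 156, and a risk-ratio margin of 0.84 gives 260. On this view the design is intact and the fault is one of drafting.

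Two further points are fair. The 99.9% figure requires the reader to insert study minus control, which is no more in the text than control minus study. It also conflicts with the 2.5% that the same sentence claims. And the literal rule passes nothing at plausible rates, so in practice it is unusable rather than lenient. The abstract's wording is a lesser matter, since the abstract also calls the trial non-inferiority and gives a margin.

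What stands is that the intent is probably control minus study and that the sample size is sound. That does not rescue the sentence. Reaching the correct rule means replacing the stated quantity with a different one, and nothing in the article makes that replacement. Nor is this a detail left to an unseen analysis plan: the article states the rule and states it wrongly, so a correct analysis plan would contradict it.

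**Conclusion.** The decision rule is wrong as written and must be corrected. It names the upper limit where the lower is needed, and the study-group rate where a between-arm difference is needed. Taken literally, it can be met only by 8 or fewer pregnancies in 98. Read as study minus control, its error at the margin is 99.9% instead of 2.5%. Only a subtraction that the text never states gives the intended 2.5% error and 80% power.

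These figures assume 98 analysed per arm and a control rate of 80%. At 108 per arm the conclusion is the same: the standard rule gives 83.8% power and about 2.6% error, and the study-minus-control upper-limit rule still passes more than 99.9% of the time at 64% vs 80%. The sample size is not in question.

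**What to change.** Replace the decision sentence in the Statistical analysis section with: non-inferiority is declared if the lower limit of the two-sided 95% CI for the difference in cumulative ongoing pregnancy rate (LH-based minus control) is greater than −16 percentage points. State H0: difference ≤ −16 points against H1: difference > −16 points, and put the same hypothesis in the abstract in place of the no-difference wording.

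This wording also settles the margin as absolute, and the amendment should say so. The current sentence calls the margin relative, but the 196 follows from 16 absolute points; 16% of 80% would be 12.8 points and would need 308 women. The interval should be described as a one-sided 2.5% test.

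The cost is one sentence in the protocol, matched in any analysis plan, with no new data and no change in sample size. It should be made and dated before the outcome data are analysed by arm.

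### The non-inferiority margin is derived and sized as 16 absolute points, but the decision rule calls it relative; under the rule as written, power is about 61% to 68% instead of 80%

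*Protocol article*

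**What the plan says.** All places are in the protocol article.

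- **Sample size calculation:** the control arm's rate is given as "the cumulative ongoing pregnancy rate per cycle in women with PCOS in the control arm was around 80" per cent. The margin follows from the statement that "a non-inferiority threshold should retain 80% of the clinical effect of a control treatment, a minimum clinical difference of 16" per cent applies. The stated result is 196 evaluable women, or 216 after allowing for 10% withdrawal. The abstract gives the same derivation.
- **Statistical analysis, the sentence before the rule:** the derivation is repeated, ending with "the minimum clinical difference should be 16" per cent.
- **Statistical analysis, the rule itself:** non-inferiority is declared if the upper limit of a two-sided 95% CI, described as belonging to the study group's pregnancy rate, "does not exceed a relative margin of 16" per cent.
- **Statistical analysis, effect measure:** "We will also compute the unadjusted risk ratio (RR) and its 95% confidence interval (CI"). This is the only between-arm estimate that the article names with an interval.

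**The concern.** Sixteen per cent means different things on the two scales. A fall from 80% to 64% is 16 points absolute and 20% relative (RR 0.80). A relative loss of 16% from 80% ends at 67.2%, which is 12.8 points or RR 0.84. The derivation and the rule therefore name different margins, in adjacent sentences, and nothing in the article reconciles them.

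This is the primary success criterion of a non-inferiority trial. If the rule is applied as written, the stated 80% power does not belong to it. If the scale is left open, it could be settled after the results are known, and a plausible result could be declared non-inferior on one scale and not on another.

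A related wording problem concerns what the margin means. The text speaks of retaining 80% of a clinical effect, but the figure being retained is the control arm's raw pregnancy rate. The article gives no effect of the control protocol over a comparator, so the margin cannot be described as preserving part of one.

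**Working it through.** **Inputs.** Control rate 80% (Sample size calculation). LH-based rate under the alternative: not stated; taken as 80%, in line with the abstract's hypothesis that "there is no significant difference in cumulative ongoing pregnancy rates between PCOS patients" in the two arms. Allocation 1:1, power 80%, 196 evaluable women, so 98 per arm. Significance level: one-sided 2.5%, which corresponds to the two-sided 95% CI in the rule. (The article labels its alpha as two-sided 2.5%. Taken literally, that gives a total of 238, so it is not what produced 196.)

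**1. Reproduce the plan's figure.** On the risk-difference scale, with margin m:

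n per arm = (1.96 + 0.8416)² × 2 × 0.8 × 0.2 / m² = 7.849 × 0.32 / m²

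- m = 0.16: 98.1 per arm, 196.2 in total. This matches 196 (strict rounding up gives 99 per arm, 198).
- m = 0.128: 153.3, so 154 per arm, 308 in total. No match.

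On the log risk-ratio scale, the variance is 2 × (0.2/0.8)/n = 0.5/n:

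- RR 0.84: 7.849 × 0.5 / (ln 0.84)² = 7.849 × 0.5 / 0.1744² = 129.1, so 130 per arm, 260 in total. No match.

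Of these three margins, only the absolute 16 points gives the stated size.

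**2. Power at 98 per arm.**

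Risk difference: SE = √(0.32/98) = 0.0571; power = Φ(m/SE − 1.96).

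- 16 points: Φ(2.80 − 1.96) = 80.0%
- 12.8 points: Φ(2.24 − 1.96) = 61.0%

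Log risk ratio: SE = √(0.5/98) = 0.0714.

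- RR above 0.84: Φ(0.1744/0.0714 − 1.96) = Φ(2.44 − 1.96) = 68.5% (67.9% if tested in the linear form, LH-based rate minus 0.84 times the control rate)

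Farrington-Manning variances change the two risk-difference figures little, to 78.9% and 60.0%. If all 216 women were evaluable (108 per arm), the three powers would be 83.6%, 65.2% and 72.7%.

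**3. Can the same data give different verdicts?** Control arm 78/98; Wald 95% CI for the difference (LH-based minus traditional) and log-scale 95% CI for the ratio.

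| LH-based arm | Lower limit, difference | Lower limit, RR | 16 points | 12.8 points | RR > 0.84 |
|---|---|---|---|---|---|
| 74/98 | −15.8 points | 0.816 | pass | fail | fail |
| 75/98 | −14.6 points | 0.829 | pass | fail | fail |
| 76/98 | −13.5 points | 0.842 | pass | fail | pass |

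Counts of 74 and 75 separate the absolute margin from both relative readings. A count of 76 fails only the fixed 12.8-point reading.

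**The case against.** The strongest reply is that the word relative is a one-word slip. The sentence just before the rule derives a difference of 16%, the sample size fits that, and nowhere does the article mention 12.8 points, 67.2% or RR 0.84. This is probably right about intent, and a reader should not infer that a second margin was deliberately designed or that the trial needs more patients. It does not remove the problem: the rule is the sentence that decides the trial, and it names the other scale.

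Three stronger readings are tempting and are not supported.

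- **That power is simply 61%.** This figure turns the ratio into a fixed 12.8-point difference, which is exact only at a control rate of 80%, and the article says around 80%. Tested as a ratio, power is about 68%. The range is the fair statement.
- **That naming the risk ratio shows the rule will be applied as RR above 0.84.** The article introduces the ratio as an additional computation and does not tie it to the rule. It leaves that application possible and no more.
- **That a positive result would be reported as preserving 80% of the control's effect.** No passage says how the result will be worded. What stands is that the phrase does not describe this margin.

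It is also fair to object that deleting one word is not enough. The rule uses an upper limit, whereas for a favourable outcome and a difference of LH-based minus traditional the lower limit decides. It also refers to an interval for one arm's rate, not for a between-arm difference. That objection is accepted, and the fix covers both points.

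**Conclusion.** The point holds. The margin was derived and sized as 16 absolute points, and the decision rule states a relative 16%. As written, the rule has power of about 61% (fixed 12.8 points) to 68% (RR above 0.84) at 98 per arm, against the planned 80%, and results two to four pregnancies apart can change the verdict with the scale. The figures rest on a control rate of 80%, no true difference, one-sided 2.5% and normal approximations. The contradiction itself rests on none of these. It should be corrected before analysis because it concerns the primary success criterion.

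**What to change.** 1. Delete the word relative and state one margin on one scale throughout: an absolute risk difference of −16 percentage points.
2. Restate the rule: non-inferiority is declared if the lower limit of the two-sided 95% CI for the risk difference (LH-based minus traditional) in cumulative ongoing pregnancy rate is above −16 percentage points. The risk ratio with its CI is supportive.
3. Replace the phrase about retaining a clinical effect with what the margin accepts: up to 16 fewer ongoing pregnancies per 100 women (80% to 64%).
4. Record this as an amendment before any comparative outcome data are seen, stating that 196 was calculated on the absolute margin. Timing matters: the article reports more than 180 women enrolled, treating physicians who are not blinded and a planned interim analysis.

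**Cost:** wording in the abstract and the sample size and analysis sections, plus one amendment; no more patients. The small downside is that the absolute margin is easier to meet than the relative one now written, so the amendment should say so openly.
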